**Methods:**

This is a prospective, randomized, multicentre superiority trial (*n* ≥ 5). Patients with active NVUGIB will be randomized (1:1) to ST and to experimental therapy (ET) by application of bipolar haemostatic forceps.

In the case of failed initial treatment within 15 min, crossover treatment will be attempted first. Rescue treatment (e.g. via over-the-scope-clip) will then be allowed after 30 min. All patients will also receive standard therapy with proton pump inhibitors. Forty-five patients per treatment arm are required to demonstrate an absolute difference of 25.4% with a power of 80% and a significance level of 0.05.

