### Trial design {8}

The trial design is as follows: prospective, multicentre superiority trial with 1:1 randomization of standard therapy versus experimental therapy.

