#### Secondary and other outcomes

Type and number of therapy-associated adverse eventsPeriod: 30 daysMeasurement method: description and countExplanation: parameters of safety of haemostasis methodsNumber and success of crossover treatmentPeriod: 30 min after localization of the source of bleedingMeasurement method: counting and assessment by the endoscopist: yes/noExplanation: further method to assess the efficacy of the haemostasis intervention with due regard to patient safetyType, number, and success of rescue treatmentPeriod: up to 6 h after localization of the source of bleedingMethod of measurement: assessment, counting and evaluation by the investigator: yes/noExplanation: Further method to assess the efficacy of the haemostasis intervention with due regard to patient safetyNumber of endoscopic reinterventionsPeriod: 30 days after initial successful endoscopic haemostasisMeasurement method: count of further endoscopic haemostasis procedures performedExplanation: indirect test of the effectiveness of the primary haemostasis methodNumber of blood units transfusedPeriod: 30 days after successful initial haemostasisMethod of measurement: count of infused blood units (transfusion unit) per patientExplanation: indirect test of the effectiveness of the primary haemostasis methodLength of hospital stayPeriod: 30 days after successful initial haemostasisMeasurement method: count of hospital days rounded up to the nearest whole dayRationale: indirect assessment of the effectiveness of the primary haemostasis methodLength of the intensive care unit (ICU) stayPeriod: 30 days after successful initial haemostasisMethod of measurement: count of the ICU days rounded up to the nearest whole dayExplanation: indirect test of the effectiveness of the primary haemostasis method30-day mortalityPeriod: 30 days after successful initial haemostasisMethod of measurement: count of patients who die during the interval, regardless of the cause of deathExplanation: indirect test of the effectiveness of the primary haemostasis methodTime until reaching complete initial haemostasisPeriod: 15 min after starting initial haemostasisMethod of measurement: time measurement in minutesExplanation: indirect test of the effectiveness of the primary haemostasis method

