### Sample size {14}

The study hypothesis is that experimental therapy is superior to standard therapy in terms of clinical success, defined as successful haemostasis and no (signs of) rebleeding within 30 days. In one study, the rates of successful haemostasis and rebleeding in the experimental group were 92.3% and 0%, respectively [9]. However, this nonrandomized trial also included nonactive nonvariceal bleeding. Therefore, the rate of successful haemostasis could be lower and the rate of rebleeding higher when only active nonvariceal bleeding is present. Therefore, a success rate of 90% for primary haemostasis and a rebleeding rate of 5% were assumed, giving a combined clinical success rate of 85.5%. In a recently published study comparing the Over-the-Scope Clip (OTSC) with the haemoclip in high-risk patients with acute nonvariceal upper gastrointestinal bleeding, the rates of successful haemostasis and rebleeding in the standard of care arm (haemoclip only) were 73.1% and 15.4%, respectively [12]. However, this randomized trial also included nonactive, nonvariceal bleeding. Therefore, the rate of successful haemostasis could be lower and the rate of rebleeding higher if only active nonvariceal bleeding is present. Therefore, a success rate of 72% for primary haemostasis and a rebleeding rate of 16% were assumed, resulting in a combined clinical success rate of 60.1%. Power analysis of the combined primary endpoint revealed that 45 patients per treatment arm are required to demonstrate an absolute difference of 25.4 percentage points (85.5–60.1%) with a power of 80% and a significance level of 0.05. Here, a simulation-based line calculation assuming the above absolute differences was performed using the SimEngine package version 1.1.0, implemented in R version 3.3.0. Overall, a dropout rate of a maximum of 10% is assumed, as the follow-up period is only 30 days. A decision on the recruitment of follow-up patients will be made when 90 patients have been included as planned and the follow-up observations are available.

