## Statistical methods

### Statistical methods for primary and secondary outcomes {20a} and for additional analyses (e.g. subgroup analyses) {20b}

An intention-to-treat analysis will be performed. Continuous variables will be reported as medians with their ranges (minimum and maximum), while categorical variables will be reported as frequencies and percentages, unless otherwise stated. For continuous variables, differences between treatment arms will be analysed using linear regression, potentially correcting for confounders such as study centre, age, anticoagulation and/or antiplatelet drugs, Forrest classification, ulcer size and location, *Helicobacter pylori* positivity, prior endoscopic treatment, and standard or bipolar haemostatic forceps therapy; categorical and binary outcomes will be analysed using logistic regression, also potentially correcting for the above confounders. Bonferroni correction will be applied to subanalyses of statistically significant tests. Corrected *p* values < 0.05 will be considered significant. Variables with a *p* value < 0.05 in the univariate model will be entered into a multivariate stepwise logistic regression model (forwards selection, likelihood ratio) to assess the independent predictive effect of the variables of interest. Statistical analysis will be performed using SPSS (version 24.0; IBM, New York, NY), Stata software (V.15; StataCorp, College Station, TX), or R (version 3.3.0 or newer).

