### Adverse event reporting and harms {22}

Adverse events (AEs) will be documented at the start of oral endoscope insertion and will end 30 days after the first haemostatic procedure. The type and number of adverse events are secondary outcome variables as defined above. Subsequent adverse events may no longer be directly related to details of the study or procedure. Overall, adverse events attributable to ST or ET are expected to be rare [3, 9]. An adverse event is defined as a serious adverse event (SAE) if it is fatal, life-threatening, or results in permanent or severe disability or incapacity. If an adverse event is classified as serious, it will be documented on a separate SAE form in addition to the AE documentation in the CRF. Patients will be asked at the 30-day query if any adverse or serious adverse events occurred. Adverse events will be documented in the CRF with the following parameters: date and time of occurrence and cessation, association with trial therapy, and outcome of the adverse event. Conditions that existed prior to the administration of the investigational product will be documented not as adverse events but as concomitant conditions. Any new disease or any disease that increases in severity during the trial shall be documented as an adverse event. Each adverse event shall be assessed by the investigator as to whether a relationship to the intervention can be suspected. The nature and pattern of the reaction, the temporal relationship with the intervention, the clinical condition of the patient, concomitant medication, and other relevant clinical parameters should be considered. If the event occurs due to lack of efficacy or due to the underlying disease, it shall be considered independent.

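### Five secondary outcomes, including 30-day mortality, start their clock at successful initial haemostasis, so on the literal wording patients whose allocated treatment fails have no defined start

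*Protocol article*

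**What the plan says.** Secondary and other outcomes gives each outcome a period. For transfused units, hospital stay, ICU stay and 30-day mortality it is "30 days after successful initial haemostasisMethod of measurement". For endoscopic reinterventions the start is the same, except that the success must be endoscopic.

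Three places indicate what initial means:
- The abstract's Methods paragraph says "In the case of failed initial treatment within 15 min, crossover treatment will be attempted first", so initial treatment is the first attempt and ends before crossover.
- Secondary and other outcomes gives time to complete initial haemostasis a 15-minute period.
- Objectives {7} uses the same term for the first half of the primary endpoint.

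The statistical methods section {20a}/{20b} states "An intention-to-treat analysis will be performed" and gives no other time origin. Adverse event reporting and harms {22} uses a different clock: documentation begins when the endoscope is inserted and "will end 30 days after the first haemostatic procedure". Crossover and rescue treatment are timed from localisation of the bleeding source.

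**The concern.** For rebleeding, the success-based start does no harm. A patient without initial haemostasis is already a failure on the combined primary endpoint, so nothing is lost when the rebleeding clock never starts.

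That logic does not carry over to death, transfusion or length of stay. There, a patient without a start date falls outside the definition and is not scored as a poor result. If the definition were applied as written, the arms would be compared only among patients in whom the allocated method worked, which is a subset chosen by the treatment itself. The plan describes these outcomes as indirect tests of the haemostasis method's effectiveness, yet the patients in whom failure would show are the ones with no window. Because failure is expected to be unequal between arms, so is the removal.

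**Working it through.** **Inputs.** From Sample size {14}: experimental arm, "a success rate of 90% for primary haemostasis and a rebleeding rate of 5% were assumed, giving a combined clinical success rate of 85.5" percent; control arm, "a success rate of 72% for primary haemostasis and a rebleeding rate of 16% were assumed, resulting in a combined clinical success rate of 60.1" percent; and "45 patients per treatment arm are required to demonstrate an absolute difference of 25.4 percentage points (85.5–60.1%) with a power of 80" percent. Significance level 0.05, sidedness not stated (two-sided assumed here). Allocation is 1:1 (Trial design {8}).

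**The plan's own figures.**
- Experimental combined success: 0.90 × 0.95 = 0.855, as stated.
- Control combined success: 0.72 × 0.84 = 0.605, against 60.1% stated. This small discrepancy has no bearing on the present point.
- Sample size from 85.5% and 60.1%, unpooled variance, two-sided: (1.960 + 0.842)² × (0.855 × 0.145 + 0.601 × 0.399) / 0.254² = 44.3, rounded up to 45 per arm, as stated. The pooled-variance formula gives 47.

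The combined rates are built as primary haemostasis times freedom from rebleeding, so the plan's failure rates for the first step are 1 − 0.90 and 1 − 0.72.

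**Patients without a start date, literal reading.**

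| | Control | Experimental |
|---|---|---|
| Initial failure rate | 28% | 10% |
| Expected failures of 45 | 0.28 × 45 = 12.6 | 0.10 × 45 = 4.5 |
| With a defined window | 32.4 | 40.5 |

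The ratio of failure rates is 0.28 / 0.10 = 2.8. In total 12.6 + 4.5 = 17.1 of 90 patients (19%) have no start. With the published haemostasis rates from which the plan started (73.1% and 92.3%), the ratio is 26.9 / 7.7 = 3.5.

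**What the definition could hide (illustration).** The documents give no mortality rates. Assume 30-day mortality s after initial success and f after failure, the same in both arms, with s between 3% and 5% and f between 10% and 30%. Then:
- Control, all randomised: 0.72s + 0.28f
- Experimental, all randomised: 0.90s + 0.10f
- Difference, control minus experimental: 0.18 × (f − s)

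Smallest: 0.18 × (0.10 − 0.05) = 0.9 percentage points. Largest: 0.18 × (0.30 − 0.03) = 4.9 percentage points. Among initial successes both arms show s, so the difference is zero throughout.

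Deaths outside the definition would be 12.6f = 1.3 to 3.8 in control and 4.5f = 0.5 to 1.4 in the experimental arm.

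The zero follows from assuming equal mortality within each stratum. In practice the 72% and the 90% who succeed are differently selected groups, so the comparison among successes could also be shifted in a direction that the documents do not let one predict.

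**A smaller effect among successes.** Units transfused before haemostasis is reached also fall outside the written window.

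**The case against.** **The term may be meant more loosely.** Objectives {7} speaks of salvage by over-the-scope clip, coiling or surgery for primary haemostasis, which suggests control of the index bleed by whatever means. On that reading nearly every patient has a start date, and 12.6 against 4.5 does not apply. This stands as a limit on the size. It does not remove the point: the 15-minute period and the abstract favour the first-attempt reading, a bleed that is never controlled still has no start, and for reinterventions the success must be endoscopic, so control by coiling or surgery would not start that clock.

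**A reader might infer that deaths after failed treatment will be lost.** The documents do not support this. The 30-day contact in {18b} is not limited to successes. Section {22} follows adverse events to 30 days after the first procedure and classes a fatal event as serious, and every serious event is reported whatever its presumed cause. Objectives {7} lists 30-day mortality with no success condition.

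**A reader might infer that the plan will drop failures from the analysis, or that mortality would come out in the wrong direction.** Neither is stated. Intention-to-treat keeps these patients in the analysis set; what is missing is their time origin. A reversal arises only if failures stay in the denominator and are scored as event-free. With s = 3% that gives 0.90 × 3% = 2.7% against 0.72 × 3% = 2.2%, about 1.2 against 1.0 expected deaths in 45. The plan describes no such analysis.

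**These are secondary outcomes.** True, and it settles the severity. The trial is powered only for the combined primary endpoint, in which initial failure already counts as failure.

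**Conclusion.** The point holds as a fault in the outcome definitions. Five secondary outcomes take their start from a post-randomisation event that treatment affects. Read literally, about 28% of control and 10% of experimental patients have no defined window; on the looser reading the number is far smaller, and the documents do not allow it to be calculated. The definitions need to be reconciled with the intention-to-treat statement and the adverse-event clock.

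The failure rates are the plan's own planning assumptions. The possible masking of a mortality difference of 0.9 to 4.9 percentage points rests on assumed mortality that is not in the documents, taken as equal across arms. It shows how the definition could mislead and is not a forecast.

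The primary endpoint and the sample size are unaffected. This is a correction to secondary outcomes that should be made before analysis, and it falls below must-fix.

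**What to change.** - For 30-day mortality, transfused units, hospital stay and ICU stay, start the 30-day period at randomisation, or at the first haemostatic procedure as already used for adverse events, for every randomised patient.
- For endoscopic reinterventions, use the same start but count only procedures after the index endoscopy session. Exclude crossover and rescue treatment, which are already separate outcomes; otherwise moving the start would count them twice.
- Leave the rebleeding window in the primary endpoint as it is.

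The cost is a change of wording in the outcome list, with matching instructions for the case report form and the analysis. The information comes from the hospital stay and the 30-day contact already planned, and no extra patients or visits are needed. Replacing length of stay by days alive and out of hospital would be a separate choice of endpoint with its own trade-offs; this correction does not require it.

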### Participant timeline {13}

The time schedule of enrolment, interventions, and assessments are shown in a schematic diagram (Table 1).

**Table 1 Tab1:**
[figure not shown]
Participant timeline. Haemoclip + / − epinephrine injection and bipolar haemostatic forceps are only used as crossover treatment if successful haemostasis has not been achieved after 15 min (X). Rescue therapy (OTSC, coiling, surgery) is only applied if successful haemostasis has not been achieved after a further 15 min by crossover treatment (X)

### Sample size {14}

The study hypothesis is that experimental therapy is superior to standard therapy in terms of clinical success, defined as successful haemostasis and no (signs of) rebleeding within 30 days. In one study, the rates of successful haemostasis and rebleeding in the experimental group were 92.3% and 0%, respectively [9]. However, this nonrandomized trial also included nonactive nonvariceal bleeding. Therefore, the rate of successful haemostasis could be lower and the rate of rebleeding higher when only active nonvariceal bleeding is present. Therefore, a success rate of 90% for primary haemostasis and a rebleeding rate of 5% were assumed, giving a combined clinical success rate of 85.5%. In a recently published study comparing the Over-the-Scope Clip (OTSC) with the haemoclip in high-risk patients with acute nonvariceal upper gastrointestinal bleeding, the rates of successful haemostasis and rebleeding in the standard of care arm (haemoclip only) were 73.1% and 15.4%, respectively [12]. However, this randomized trial also included nonactive, nonvariceal bleeding. Therefore, the rate of successful haemostasis could be lower and the rate of rebleeding higher if only active nonvariceal bleeding is present. Therefore, a success rate of 72% for primary haemostasis and a rebleeding rate of 16% were assumed, resulting in a combined clinical success rate of 60.1%. Power analysis of the combined primary endpoint revealed that 45 patients per treatment arm are required to demonstrate an absolute difference of 25.4 percentage points (85.5–60.1%) with a power of 80% and a significance level of 0.05. Here, a simulation-based line calculation assuming the above absolute differences was performed using the SimEngine package version 1.1.0, implemented in R version 3.3.0. Overall, a dropout rate of a maximum of 10% is assumed, as the follow-up period is only 30 days. A decision on the recruitment of follow-up patients will be made when 90 patients have been included as planned and the follow-up observations are available.

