## Discussion

The hypothesis of the study is that bipolar haemostatic forceps are superior to standard therapy with haemoclip + / − epinephrine injection in terms of successful primary haemostasis and the absence of recurrent bleeding within 30 days (combined endpoint). In a nonrandomized Japanese trial, the rate of successful primary haemostasis was 92.3%, and the rate of recurrent bleeding was 0% for bipolar haemostasis forceps [9]. However, active, nonvariceal bleeding was not considered in this study. Accordingly, successful primary haemostasis is expected to be somewhat lower and recurrent bleeding rates somewhat higher, as the method was used exclusively for active, nonvariceal bleeding in the BeBop study. In contrast, the rates of successful haemostasis and recurrent bleeding with standard therapy were 73.1% and 15.4%, respectively, in a recently published study in which the over-the-scope clip (OTSC) was the experimental arm [3]. This study also included nonactive, nonvariceal bleeding, so successful primary haemostasis may be lower and repeat bleeding rates higher when treating active, nonvariceal bleeding. The expected difference in success rate between the two procedures with respect to the combined endpoint was therefore calculated to be 25.4%, which is the basis for the case number calculation (*n* = 90). The 1:1 randomization is also ethically justifiable for this study, as both procedures are approved for the intervention in question. To further increase the safety of the patients in the study, crossover treatment and rescue treatment are planned. The prospective design seems feasible in a reasonable time frame (recruitment period of 12 months), as nonvariceal upper gastrointestinal bleeding is common [1]. Therapy with anticoagulants, antiplatelet agents, or a combination of the two is often associated with gastrointestinal bleeding [18, 19]. Therefore, anticoagulants and/or antiplatelet drugs could be an important confounding factor in the statistical analysis that needs to be considered and calculated if necessary [20]. Tumour haemorrhage is usually accompanied by diffuse bleeding at several sites and haemostasis by clip or haemostatic forceps did not appear to be promising. Therefore, tumour haemorrhage was not included in the study as it could bias the statistical results. In consequence, this study cannot make a reliable statement about the use of haemostasis forceps in terms of haemostasis of tumour bleeding in the upper gastrointestinal tract. In conclusion, this randomized, prospective, multicentre study could make an important contribution to answering the question of whether bipolar haemostatic forceps could be the first-line therapy in the endoscopic treatment of upper gastrointestinal nonvariceal bleeding stage Forrest I a + b.

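### 45 per arm gives 80% power only if all 90 patients are evaluable: the assumed 10% dropout was not allowed for (power then about 74–76%), and the control rate should be 60.5%, not 60.1%

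*Protocol article*

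**What the plan says.** All references are to the protocol article.

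- **Endpoint (Sample size {14}):** the trial is powered on "clinical success, defined as successful haemostasis and no (signs of) rebleeding within 30 days", a binary composite.
- **Experimental arm (same section):** "a success rate of 90% for primary haemostasis and a rebleeding rate of 5% were assumed, giving a combined clinical success rate of 85.5"%.
- **Control arm (same section):** "a success rate of 72% for primary haemostasis and a rebleeding rate of 16% were assumed, resulting in a combined clinical success rate of 60.1"%.
- **Result (same section):** 45 per arm for a difference of 25.4 points, "with a power of 80% and a significance level of 0.05". The number came from simulation. Neither the simulated test nor the sidedness is given.
- **Dropout (same section, after the number is derived):** "Overall, a dropout rate of a maximum of 10% is assumed, as the follow-up period is only 30 days". The next sentence says that a decision on recruiting further patients will be taken once the planned 90 are included and followed up. It gives no number, trigger or rule.
- **Recruitment {15}:** the target is 90 in 12 months, and centres may be added to reach it.
- **Repeats:** the abstract has "Forty-five patients per treatment arm are required to demonstrate an absolute difference of 25.4% with a power of 80"%. The Discussion says that the difference "was therefore calculated to be 25.4%, which is the basis for the case number calculation", with n = 90.
- **Missing data {20c}:** none is expected, which does not sit well with an assumed dropout of up to 10%.

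**The concern.** A power calculation gives the number of patients whose outcome must be known. If up to 10% are assumed lost, enrolment has to exceed that number, or the power has to be stated for the smaller number analysed. The article does neither. It computes 45 per arm, assumes the loss, and plans for 90.

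The two combined rates also look as if they follow different rules. The experimental rate is exactly the product of its components. The control rate is not, and the discrepancy enlarges the planned difference.

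At stake is how a non-significant result would be read. This is the only power statement for the primary comparison, and a reader would set a null result against a type II error of 20%. Under the plan's own dropout assumption it would be nearer 25%.

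**Working it through.** **Inputs (Sample size section).** Haemostasis 90% and rebleeding 5% (experimental); 72% and 16% (control); significance level 0.05; power 80%; 45 per arm; dropout up to 10%. Two-sided testing and an unadjusted comparison of two proportions are my assumptions.

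**1. Combined rates.** Success = haemostasis × (1 − rebleeding).
- Experimental: 0.90 × 0.95 = 0.855, as stated.
- Control: 0.72 × 0.84 = 0.6048, stated as 0.601.
- Difference: 0.855 − 0.6048 = 0.2502, stated as 0.254.

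**2. Reproducing 45 per arm at the stated rates.** Unpooled normal formula: n = (1.960 + 0.842)² × [p₁(1 − p₁) + p₂(1 − p₂)] / (p₁ − p₂)².
- At 0.855 vs 0.601: 7.849 × 0.3638 / 0.0645 = 44.3, so 45.
- The pooled formula gives 47.
- Exact enumeration of the two binomials with the Pearson chi-square test gives 80.05% power at 45/45.

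The published figure therefore reproduces, with all 90 analysed and nothing held back for dropout.

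**3. Effect of the control rate alone (0.6048, 45/45 analysed).**
- Exact chi-square: 79.0%, down from 80.05%.
- Pooled normal formula: 77.1%, down from 78.2%.
- Unpooled normal formula: 79.6%, which still rounds to 80%.

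**4. Effect of dropout.** 90 × 0.90 = 81 analysed, split 41/40 or 40/41. The exact range shows which arm has 41; the pooled formula uses 40.5 per arm.

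| Control rate | Exact chi-square | Pooled normal |
|---|---|---|
| 60.1% (as stated) | 74.7–75.7% | 73.7% |
| 60.48% (corrected) | 73.6–74.6% | 72.6% |

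**5. A milder form of loss.** A patient without haemostasis at 15 minutes is already a composite failure, so later dropout cannot remove that outcome. Suppose that 10% of patients with initial haemostasis are lost.
- Expected evaluable, experimental: 45 × (1 − 0.90 × 0.10) = 40.95.
- Expected evaluable, control: 45 × (1 − 0.72 × 0.10) = 41.76.
- Exact chi-square power, averaged over the evaluable numbers with the 72%/16% inputs: about 76%. With 5% loss it is about 77%.

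**6. Enrolment that would restore 80% power (both corrections, for information).**
- Unpooled formula: 46 evaluable; 46/0.9 = 51.1, so 52 per arm.
- Exact chi-square: 47 evaluable gives 79.8% and 48 gives 80.9%; 48/0.9 = 53.3, so 54 per arm.
- Pooled formula: 49 evaluable; 49/0.9 = 54.4, so 55 per arm.

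**The case against.** **The stated power is not false on its face.** The article says that 45 per arm are required for 80% power, and for evaluable patients at the stated rates that is right. It never claims 80% after 10% loss. This stands: a reader might infer that the 45 is a miscalculation, but it is not. The fault is that evaluable and enrolled numbers are treated as one.

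**Dropout may be handled by topping up.** The sentence after the dropout assumption can be read as replacement of losses, so 90 is not shown to be a fixed cap. This stands in part. The sentence leaves a discretionary decision, made after follow-up observations are available, without number or rule. That is no planned allowance. The option to add centres serves only to reach 90.

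**The loss may be smaller.** The 10% is a stated maximum, and early failures cannot lose their outcome. This stands, and it is why the range runs up to 76%. A reader might also go the other way and score every lost patient as a failure, which would lower power further. The article states no such rule, so that reading is not supported.

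**The control-rate slip is immaterial.** It moves the rate by 0.4 points and power by about 1 point, and under the unpooled formula power still rounds to 80%. It might also come from unrounded inputs (0.716 × 0.84 = 0.601), but the article gives only 72% and 16%. It is a minor correction, and a reader should not infer that it undermines the design.

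**Conclusion.** The point holds, with the dropout allowance as its substance. The planned enrolment of 90 does not deliver the stated 80% power under the article's own assumption of up to 10% dropout. At that maximum and the corrected control rate, power is about 74–76%: 73.6–74.6% with 81 analysed, and about 76% if only patients with initial haemostasis can be lost. The pooled normal formula gives about 72–73%. The control rate and planned difference should read 60.5% and 25.0 points, which is an error of little consequence by itself.

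These figures assume a two-sided 0.05 test, an unadjusted comparison, similar loss in both arms, and lost patients left out of the analysis. The power figures change with the test, which the article does not name. The missing allowance and the product 0.72 × 0.84 do not depend on it.

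**What to change.** 1. In Sample size, change the control rate from 60.1% to 60.5%.
2. In the abstract (Methods), Sample size and Discussion, change the difference from 25.4 to 25.0 points.
3. In Sample size, state that the power refers to 45 evaluable patients per arm (80% as first calculated, about 79% at the corrected rate), and that 90 randomised with up to 10% loss gives roughly 74–76%. Name the test and the sidedness behind these figures.
4. If an enrolment figure is given for information, use about 52–55 per arm with both corrections and name the formula or test. Dividing 45 by 0.9 would carry the uncorrected control rate forward.

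The cost is wording only. No change to enrolment, endpoint or analysis is required; the stated power simply becomes less favourable.
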